## Methods

In this section, the VA DPP evaluation aims, study participants, data collection procedures, and analysis plans will be described for each study aim.

### Aim 1: implementation evaluation

This study will not be sufficiently powered to quantitatively assess site-specific factors that may influence implementation outcomes. Therefore, this study will conduct a mixed methods, multi-dimensional, formative evaluation of the implementation strategy. This formative evaluation will incorporate the following features: 1) developmental evaluation to identify barriers and facilitators to implementation; 2) implementation and progress-focused evaluation to actively monitor implementation progress and adapt the program as needed; and 3) interpretive evaluation to provide detailed information on success or failure of implementation [20]. If the program is effective in the Veteran population, findings will be used to develop recommendations for disseminating the VA DPP more broadly in the VA.

#### Evaluation framework

This study will integrate two published frameworks to guide the formative evaluation: 1) the RE-AIM framework [21] will be used to assess external validity and prospects for dissemination and implementation of the VA DPP in the VA and 2) the Consolidated Framework for Implementation Research (CFIR) will be used to systematically assess contextual factors that influence adoption and implementation [22]. Figure 2 illustrates the integration of RE-AIM and CFIR. Additional file 2 provides detailed research questions and quantitative and qualitative measures for each of the RE-AIM dimensions.

**Figure 2 Fig2:**
[figure not shown]
Formative evaluation framework: integration of RE-AIM and the CFIR.

The CFIR will be used to guide a systematic evaluation of barriers and facilitators that may affect adoption, implementation, and/or maintenance. The CFIR comprises 39 common constructs from across published implementation frameworks and models that are believed to influence implementation [23-25]. These constructs are organized within five major domains: intervention characteristics, outer and inner setting, characteristics of individuals, and implementation process. Examples of constructs include the relative advantage of the program (intervention characteristics), patient needs and resources (outer setting), networks and communications in the facility (inner setting), knowledge and beliefs of stakeholders (characteristics of individuals), and engaging stakeholders in the process (process).

#### Study participants

Participants will include VA DPP staff, VA MOVE! program coordinators and staff, Health Promotion and Disease Prevention (HPDP) program managers, Health Behavior Coordinators (HBC), primary care clinical leaders, primary care providers, and other primary care staff at each VA DPP site.

#### Data collection

##### Staff interviews

The CFIR will be used to develop a semi-structured interview guide and guide data collection. Additional file 3 provides copies of the staff interview guides. Stakeholders (four to ten per site) will be interviewed at early (or pre-) implementation and late (or post-) implementation of the VA DPP. Interviews will take place over the phone or in person during site visits and will last 15–60 min. The early implementation interviews will assess receptivity to the VA DPP and identify potential implementation barriers and facilitators. This information will be used to develop tailored implementation and communication strategies for each site. The late implementation interviews will elicit in-depth information about experiences implementing and administering the VA DPP and to understand success or failure of implementation. These interviews will explore prospects for sustainability and inform broader dissemination and implementation if the program is effective. In addition, field notes, project meeting notes, and other artifacts (e.g., emails) will be used throughout the course of the study in order to identify and address barriers to implementation, refine the program, and provide feedback to site staff.

##### Fidelity assessments

Fidelity checklists will be completed for two VA DPP and two VA MOVE! sessions in each cohort. The project coordinator will use the checklist to rate each item and provide open-ended notes. This approach will provide fidelity assessments of VA DPP delivery and a comparison to VA MOVE! sessions. Additional file 4 provides copies of the fidelity checklists.

#### Data analysis

##### Staff interviews

The CFIR will be used as an organizing framework for qualitative data coding and analysis. Deductive and inductive content analyses, guided by a consensus-based qualitative research approach [26,27], will be conducted on all interview data using NVivo qualitative analysis software. This analysis approach will have the following features: 1) multiple judges will be used throughout data analysis to foster multiple perspectives; 2) consensual validation will be achieved through a process of discussion and deliberation [28]; 3) an expert auditor not integrally involved in the study will review the process to help maximize validity of findings; and 4) CFIR constructs will be identified and applied to cases, and cross-analyses will be performed [29]. A summary will be written for each facility based on data from verbatim interview transcripts and field notes with supporting quotes. Matrices will be constructed to help discern patterns within and across facilities by comparing and contrasting themes. Qualitative analysts will be blinded to facility outcomes related to implementation effectiveness until qualitative data analyses are completed. Full information from all facilities will be used in the interpretative phase, when qualitative findings will be combined with quantitative data measuring implementation effectiveness.

##### Fidelity assessments

Fidelity ratings will be used to compute average scores for coaching and delivery fidelity domains. Simple *t*-test analyses will be used to assess differences between the VA DPP and VA MOVE!.

### Aim 2: effectiveness evaluation

This study will evaluate whether patient weight and A1c outcomes are better in the VA DPP than those in VA MOVE!. In addition, process measures will be assessed, including the percentage of Veterans who engage in (attend at least four sessions) and adhere to (attend at least nine sessions) the VA DPP [30]. Careful attention will be paid to discern whether there are significant differences across important demographic sub-groups, such as gender or race/ethnicity in program outcomes (weight and A1c outcomes) or process measures (enrollment, engagement, and adherence). Mediation analyses will also be conducted to identify whether program design differences between the VA DPP and VA MOVE! impact outcomes.

#### Study participants

Participants will include eligible Veterans who are referred to VA MOVE! at each of the three VA DPP sites. Table 4 details eligibility criteria. Power analyses were conducted to determine sample size needed to have 80% power to detect expected differences in program outcomes with alpha of .05, assuming two-tailed testing. The power analysis assumed that the VA DPP would result in 1.7 additional pounds of weight loss compared to VA MOVE! with a standard deviation of 6.96 lbs (assuming a standard deviation of 11 lbs and a within-person correlation of .8 for weights at baseline versus 12 months) and assuming an intra-group correlation coefficient of .014. Assuming that 20% of participants would drop out by 12 months, this calculation indicated the need to recruit 720 patients (360 for the VA DPP and 360 for VA MOVE!). Given the sample size, the expected pace of recruitment, a target of 20 participants per cohort, and the structure of the existing VA MOVE! programs, six cohorts will be conducted with a new cohort starting every 2 months. Since randomization is not possible for this clinical demonstration, a systematic assignment process will be used; every 2 months, the first 20 patients who meet the VA DPP eligibility criteria will be enrolled and assigned to the VA DPP and the next 20 eligible patients will be assigned to VA MOVE! by VA DPP site staff.

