#### Phase three: implementation (exploratory use)

VA DPP cohorts will run in parallel to existing VA MOVE! groups. Implementation will rely on the existing VA MOVE! infrastructure for obesity screening, program referral, and medical clearance. Each site will develop a site-specific protocol that aligns the new processes for screening, identifying, informing, and assigning Veterans to the VA DPP within the existing VA MOVE! infrastructure. Protocols will also include processes for using the electronic medical record (EMR) system to track Veterans with prediabetes by VA DPP cohort. These institutional supports will be essential for monitoring and providing feedback to ensure successful implementation and administration of the VA DPP. The research coordinating center will facilitate weekly calls with VA DPP staff from each site to get status updates and provide collective problem-solving support during the implementation process.

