#### Data analysis

##### Patient surveys and clinical outcomes

Effects of the VA DPP and VA MOVE! on patient outcomes at 12 months will be assessed using clinical weights and A1c lab values. The distribution of all study variables and baseline differences in factors that may affect study outcomes between groups will be assessed. If significant differences are found, they will be included as covariates in the final analyses. At each assessment time, cross-sectional means and their associated 95% confidence intervals for continuous outcomes (e.g., weight) will be described. Comparison between the VA DPP and VA MOVE! in weight loss at 12 months will be completed with a linear mixed-effects model, using program arm as random intercepts to account for potential intra-program group correlation. The model will include the primary predictor of program arm (the VA DPP or VA MOVE!), indicators for the three study sites, baseline weight values, and age, sex, and race variables. Time-averaged effects of the VA DPP over VA MOVE! will be compared using weight loss at 12 months as the dependent variable. The model will allow the use of all available data, even if some Veterans are missing 12-month weights, and will give an unbiased estimate as long as missingness does not depend on the unobserved missing outcomes. Careful graphical analyses of longitudinal outcome data will be completed to ensure that an appropriate and meaningful longitudinal model is created. Additional file 7 describes the planned mediation analyses.

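### Assignment is predictable and always fills the VA DPP first, so short cycles tie arm to enrolment period, and the 12-month weight model has no site-by-cycle term

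*Protocol article*

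**What the plan says.** The protocol article explains the choice of design under Aim 2, Study participants: "Since randomization is not possible for this clinical demonstration, a systematic assignment process will be used". The rule for each 2-month cycle begins with the intervention: "the first 20 patients who meet the VA DPP eligibility criteria will be enrolled and assigned to the VA DPP". Once those places are taken, the comparator block is formed: "the next 20 eligible patients will be assigned to VA MOVE! by VA DPP site staff". The same section plans "a target of 20 participants per cohort" and states that "six cohorts will be conducted with a new cohort starting every 2 months". No variation of the order, concealment or independent assigner is described. The section on implementation phase three leaves the local process to the sites: "Each site will develop a site-specific protocol that aligns the new processes for screening, identifying, informing, and assigning Veterans to the VA DPP".

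Under Aim 2, Data analysis, the 12-month weight model contains program arm together with "indicators for the three study sites, baseline weight values, and age, sex, and race variables", plus any baseline factor found to differ significantly between groups. The random part is described as "using program arm as random intercepts to account for potential intra-program group correlation". Neither enrolment cycle nor enrolment date appears. The Trial status section reports that recruitment and baseline assessment are complete, and that cleaning and analysis of the 12-month outcomes have not begun.

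**The concern.** There are two separate problems.

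**Predictability.** Anyone who keeps the running count knows which program the next eligible patient will enter. The date of eligibility depends on steps that people can time: Table 4 requires a laboratory result and a completed VA MOVE! introduction class, and the baseline A1c may be ordered by providers or by the VA DPP coaches. A keen or reluctant patient could therefore end up on one side of the boundary rather than the other. Age, sex, race and baseline weight would capture motivation poorly.

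**Fixed order with uneven filling.** Because the VA DPP always fills first, a shortage of eligible patients falls on VA MOVE!. If shortages differ from cycle to cycle, the two arms are spread differently over calendar time within a site. Season, changes in coaching or changes in referral practice could then enter the arm comparison. The site indicators do not address this, because the imbalance lies within site.

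At stake is the 12-month weight comparison. Its planned difference is only 1.7 lb, so a modest bias matters.

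**Working it through.** **Inputs from the article:** 3 sites; 6 cohorts; 20 per cohort; one cycle every 2 months; 360 per arm; 20% dropout; target difference 1.7 lb; SD of change 6.96 lb; intra-group correlation 0.014. **Assumed for illustration:** the filling pattern, the calendar drift, and the selection quantities x and D below.

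**1. Block structure.** 3 × 6 × 20 = 360 per arm, which matches the plan. There are 3 × 6 = 18 site-cycles, each meant to hold 20 VA DPP and 20 VA MOVE! patients. Beyond the site indicators, site-by-cycle needs 3 × (6 − 1) = 15 degrees of freedom. If every site-cycle fills, cycle is balanced across arms and cannot confound them.

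**2. Uneven filling (assumed pattern).** Suppose a site finds 30 eligible patients in each of cycles 1–3 and 40 in each of cycles 4–6.
- VA DPP: 20 per cycle; mean cycle number 3.5.
- VA MOVE!: 10, 10, 10, 20, 20, 20; mean cycle number = (10 × 6 + 20 × 15) / 90 = 360 / 90 = 4.0.
- Difference: 0.5 cycle = 1 month.

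A cycle-to-cycle drift of 0.25 lb per month would move the arm difference by 0.25 lb (0.25 / 1.7 = 15% of the target). Cycle indicators within the site reduce this component to zero. With late rather than early shortfalls the sign reverses. With the same shortfall in every cycle the component vanishes.

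**3. What a cycle term cannot remove.** With even accrual over a 2-month cycle of 40 patients, the first 20 have a mean entry time of 0.5 month and the next 20 of 1.5 months, a difference of 1.0 month. A steady drift of 0.1, 0.25 or 0.5 lb per month then gives a bias of 0.1, 0.25 or 0.5 lb. Least-squares fits gave the same bias with and without cycle indicators, because order within a cycle coincides with arm.

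**4. Scale for judging a bias.** Completers per arm: 360 × 0.8 = 288; per group: 20 × 0.8 = 16. Design effect: 1 + 15 × 0.014 = 1.21. Standard error of the difference: 6.96 × √(2/288) × √1.21 = 0.638 lb. With no true difference, a bias of 0.25 lb raises the two-sided 5% error to about 6.8%, and 0.5 lb to about 12.3%.

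**5. Steering (assumed x and D).** Let the more motivated half lose D lb more, and let them make up 50 + x% of the VA DPP and 50 − x% of VA MOVE!. Then bias = 2xD, with x as a proportion.

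| x | D (lb) | Bias (lb) | Share of 1.7 lb | Error rate |
|---|---|---|---|---|
| 2.5 points | 3 | 0.15 | 9% | 5.6% |
| 10 points | 3 | 0.6 | 35% | 16% |
| 10 points | 5 | 1.0 | 59% | 35% |

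**6. The stated random effect is no substitute.** Read literally, it is indexed by arm. If it means the individual class group, each group lies wholly within one arm, so it still does not compare arms within the same cycle.

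**The case against.** The design is openly non-randomized, implementation is the primary aim, and the article calls the internal validity acceptable given practical constraints. This stands as a reason for not randomizing. It does not explain why one program always fills first or why the analysis ignores the blocks in which the arms were formed.

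If every block fills, a cycle term affects only precision. That is correct: the confounding in step 2 depends on uneven filling, which the article neither reports nor rules out.

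Other baseline factors may enter the model, and the baseline surveys cover goal commitment and outcome expectations. This helps in part, but the surveys reach only consenting respondents, and a non-significant difference does not show balance.

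Three stronger readings are tempting and should be resisted.
- A reader might infer that the analysis ignores the arm implied by the eligibility sequence. The article does not say so. If the rule is followed, program arm is that arm; only the handling of departures is unstated, and a fuller document may cover it.
- A reader might infer a bias of 0.6–1.0 lb in favour of the VA DPP. Those figures rest on assumed x and D, and the direction is not shown. Nor does promptness necessarily follow arm: a slow responder in one cycle can be among the first 20 of the next.
- A reader might take the assigners to be the program's own coaches. The wording could equally mean staff at the demonstration sites, although either group would know the next assignment.

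**Conclusion.** The concern holds in a limited form. The article fixes a predictable order that never varies and is applied by site staff, so selection into arm is possible. Whenever eligible numbers fall short of 40 by differing amounts across cycles, arm is also associated with enrolment period, and the stated model has no term for it. (Below 20, the VA DPP is short as well and VA MOVE! is empty for that cycle.)

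The size cannot be derived from the document. The calendar component was 0.25 lb under one assumed pattern and drift, and zero if all blocks fill. The selection component ranged from 0.15 to 1.0 lb over the assumed values, with unknown direction. Only the between-cycle calendar component can be removed by analysis. Order within a cycle and any steering of eligibility timing remain, since a manipulated date is already part of the recorded sequence. The omission is worth correcting because the remedy is cheap and the 12-month analysis has not started.

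**What to change.** Specify the following before the 12-month data are analysed.

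1. Add site-by-enrolment-cycle to the 12-month weight model, with up to 18 levels. Fixed effects remove between-cycle differences fully; random effects do so only partly but use fewer parameters. Six levels shared across sites would not do, because the VA DPP design section lets site capacity set the interval between cohorts, so the same cycle number need not mean the same dates at each site.
2. State that arm is the arm assigned under the 20-then-20 rule, whatever program was attended.
3. As a check, compare the recorded order of eligibility with referral and introduction-class dates in the medical record, and report departures by site. The article describes record tracking by cohort, so whether an ordered eligibility record exists has to be confirmed first.
4. State that these steps deal with uneven filling and calendar confounding but not with order effects within a cycle or steering by staff, and have the Aim 2 conclusion acknowledge residual selection bias of unknown size and direction.

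The cost is about 15 degrees of freedom among 720 recruited patients, plus extraction of dates. A site-cycle with no VA MOVE! patients would add almost nothing to the arm comparison under fixed effects. Changing who assigns, or which program fills first, is no longer possible because patients have been recruited.

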#### Data collection

##### Patient clinical outcomes

Weight will be measured with a medical-grade scale at each VA DPP and VA MOVE! session as well as at a 12-month program-specific session. Weight will also be routinely measured and documented in the EMR during other VA clinical visits. Baseline A1c and 12-month follow-up A1cs will be ordered by providers or the VA DPP coaches. A1c testing will occur via a laboratory blood draw or point of care (POC) testing. Attendance at all VA DPP and VA MOVE! sessions will be documented in the EMR by program session leaders.

#### Patient surveys

Eligible Veterans will be invited to complete baseline surveys after completing an informed consent process. Consented Veterans will be given a paper copy of the survey along with a business reply envelope addressed to the research coordinating center. At 12 months, Veterans will be invited to complete follow-up surveys. Survey instructions will include a web address that will link to an electronic version of the paper survey for Veterans who prefer to answer the survey online. The surveys will measure potential mediators of program outcomes, including perceptions of goal awareness and commitment, outcome expectations, group cohesion, self-regulation skill mastery, and program intensity, as well as quality of life, satisfaction with the program, sleep, social support, and depression. Additional file 5 provides a copy of the program surveys.

#### Patient interviews

At 12 months, patients will be purposively selected for interviews in order to maximize variation in program arm, participation, weight loss, and sex. Table 5 illustrates the sampling strategy. Interviews will assess patient experiences in the program. Additional file 6 provides a copy of the patient interview guide.

**Table 5 Tab5:** **Sampling strategy for patient semi-structured interviews**

Axis of diversity	Strata
Program	• VA DPP
	• VA MOVE!
Level of participation	• High participation
	• Low participation
	• No participation
Category of weight loss	• High weight loss
	• Low weight loss, maintenance, or weight gain
Sex	• Women
	• Men

#### Data analysis

##### Patient surveys and clinical outcomes

Effects of the VA DPP and VA MOVE! on patient outcomes at 12 months will be assessed using clinical weights and A1c lab values. The distribution of all study variables and baseline differences in factors that may affect study outcomes between groups will be assessed. If significant differences are found, they will be included as covariates in the final analyses. At each assessment time, cross-sectional means and their associated 95% confidence intervals for continuous outcomes (e.g., weight) will be described. Comparison between the VA DPP and VA MOVE! in weight loss at 12 months will be completed with a linear mixed-effects model, using program arm as random intercepts to account for potential intra-program group correlation. The model will include the primary predictor of program arm (the VA DPP or VA MOVE!), indicators for the three study sites, baseline weight values, and age, sex, and race variables. Time-averaged effects of the VA DPP over VA MOVE! will be compared using weight loss at 12 months as the dependent variable. The model will allow the use of all available data, even if some Veterans are missing 12-month weights, and will give an unbiased estimate as long as missingness does not depend on the unobserved missing outcomes. Careful graphical analyses of longitudinal outcome data will be completed to ensure that an appropriate and meaningful longitudinal model is created. Additional file 7 describes the planned mediation analyses.

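### The 12-month weight model is specified with one outcome per Veteran, yet is credited with properties that only a repeated-measures model has

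*Protocol article*

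**What the plan says.** All the modelling statements are in the protocol article, Aim 2, under Patient surveys and clinical outcomes.

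- **Outcome and target:** "Time-averaged effects of the VA DPP over VA MOVE! will be compared using weight loss at 12 months as the dependent variable". The sentence that introduces the mixed model also names weight loss at 12 months as what is compared.
- **Random part:** "using program arm as random intercepts to account for potential intra-program group correlation".
- **Fixed part, besides arm:** "indicators for the three study sites, baseline weight values, and age, sex, and race variables".
- **Data use:** "The model will allow the use of all available data, even if some Veterans are missing 12-month weights".
- **Missing-data property:** the model "will give an unbiased estimate as long as missingness does not depend on the unobserved missing outcomes".
- **Longitudinal model:** the section then says that graphs of the longitudinal outcomes will guide the building of a suitable longitudinal model, with no further detail.

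On the data themselves, Patient clinical outcomes states: "Weight will be measured with a medical-grade scale at each VA DPP and VA MOVE! session as well as at a 12-month program-specific session". It adds that weights are also recorded in the medical record at other VA visits. Interim weights will therefore exist for many Veterans.

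**The concern.** The outcome as named and the properties as claimed belong to two different models. A likelihood-based mixed model uses a partly observed person only through the outcome rows which that person supplies. If the only outcome is the 12-month loss, a Veteran with no 12-month weight supplies no row, and baseline weight on the covariate side does not change that. An average over time also cannot come from one time point, and Aim 2 asks for the 12-month comparison.

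Two things are at stake. First, two analysts following the same section could fit different models, to different sets of Veterans, with different targets. Second, the missing-data assurance is wider than the named outcome can support. Missingness that depends on earlier observed weights satisfies the article's condition, yet those weights are not in the model.

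**Working it through.** **1. Specification against claims**

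| Stated property | What it needs | What the stated model has |
|---|---|---|
| Time-averaged effect | Outcomes at several times | One outcome, at 12 months |
| All available data used when the 12-month weight is missing | Interim weights as outcome rows, linked within person | No interim rows, no person-level term |
| Unbiased unless missingness depends on unobserved outcomes | Observed earlier weights in the likelihood | Arm, site, baseline weight, age, sex and race only |

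The stated model guarantees an unbiased contrast only under the narrower condition that missingness is unrelated to the 12-month outcome given those covariates.

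**2. Veterans excluded.** Inputs are 720 recruited and 20% dropout (Aim 2, Study participants). 720 × (1 − 0.20) = 576 enter the model, or 288 per arm, and 720 − 576 = 144 contribute nothing. This equates dropout with a missing 12-month weight.

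**3. The plan's SD.** 11 × √(2 × (1 − 0.8)) = 6.957, which reproduces the stated 6.96 lb.

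**4. Illustrative bias.** The assumptions here are not from the documents:
- 20% missing in each arm.
- The log odds of missing rise by ln(OR) per SD of poorer early loss, with OR 1.5, 2 or 3.
- The correlation ρ between early and 12-month loss is 0.5 to 0.7.
- The modelled covariates do not explain early loss.

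With z the standardised early loss, the bias in one arm's completer mean is ρ × E(z | observed) × 6.96. E(z | observed) comes from numerical integration with the intercept set to give 20% missing.

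| OR | E(z given observed) | ρ = 0.5 | ρ = 0.7 |
|---|---|---|---|
| 1.5 | 0.0790 | 0.27 lb | 0.38 lb |
| 2 | 0.1288 | 0.45 lb | 0.63 lb |
| 3 | 0.1855 | 0.65 lb | 0.90 lb |

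The bias in the arm contrast is the VA DPP value minus the VA MOVE! value:
- Same OR in both arms: 0.
- Dependence in the VA DPP only: +0.27 to +0.90 lb, which is 0.27/1.7 = 16% to 0.90/1.7 = 53% of the target difference.
- Dependence in VA MOVE! only: the same sizes with a negative sign.
- OR 2 in the VA DPP against 1.5 in VA MOVE!: (0.1288 − 0.0790) × ρ × 6.96 = 0.17 to 0.24 lb.
- OR 3 against 1.5: (0.1855 − 0.0790) × ρ × 6.96 = 0.37 to 0.52 lb.

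**5. Does using interim weights help?** A separate simulation (4,000 runs) assumed a 6-month difference of 3.0 lb, a true 12-month difference of 1.7 lb, a correlation of 0.8 between the two losses, and about 17–19% missing. With missingness unrelated to earlier loss, completers alone gave 1.69 lb. With missingness in the VA DPP arm depending on the observed 6-month loss, completers alone gave 2.17 lb (moderate dependence) or 2.70 lb (strong). An analysis that also used the 6-month weight gave 1.69 to 1.71 lb throughout. Every simulated Veteran had a 6-month weight, so this is a best case.

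**The case against.** The strongest reply is that the authors meant a repeated-measures model. Three statements point that way (the time-averaged effect, the use of all available data, and the longitudinal model), and one phrase points to a single outcome. Time windows and covariance structure are details that an article may leave to the analysis plan. This stands in part: a reader might infer that the plan has settled on a complete-case analysis, and the text does not support that. But the article does name the dependent variable, and what it names conflicts with what it claims. The longitudinal-model sentence gives no outcome vector, time term or contrast, so it shows a likely intention without resolving the conflict.

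A reader might also infer that the estimate will favour the VA DPP, since the two programs run on different schedules. No passage says that early loss drives dropout, or that it does so differently by arm. Both programs have a 12-month weighing session. The bias is therefore conditional and its sign is open.

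Three further points stand. The 20% is a dropout assumption for sample size, and a Veteran who leaves the program may still have a medical-record weight near 12 months. The missing-data statement is true of a single-outcome model under the narrower condition in step 1. And Table 5 anticipates Veterans with no participation, who would have no session weights, so a longitudinal model gains little for them.

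**Conclusion.** The point holds as an internal contradiction in the stated analysis. Taken literally, the model estimates the 12-month difference among Veterans with a 12-month weight, so none of the three properties in step 1 holds as claimed. That conclusion rests on the model's structure alone and on no simulated figure.

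The practical size is uncertain. It is nil if missingness depends only on the modelled covariates, or depends equally on earlier loss in both arms. It is about 0.3 to 0.9 lb in either direction, against 1.7 lb, if the dependence lies in one arm only and the assumptions in step 4 hold. Weight is an Aim 2 outcome and implementation is the primary aim, but this is the effectiveness comparison on which the sample size rests. Under Trial status, cleaning and analysis of 12-month outcomes had not begun, so the text could be settled before results were seen.

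**What to change.** Preferred: make the repeated session and medical-record weights the outcome, in the same prespecified time windows for both arms. Include arm, time, arm-by-time, baseline weight, the covariates already listed, within-person correlation and the group random intercept. Name the arm contrast at 12 months as the primary estimate and delete the reference to time-averaged effects.

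Alternative: keep the single 12-month outcome, multiply impute missing values using the interim weights, delete the reference to time-averaged effects, and withdraw the statement that the model itself uses all available data. Limit the unbiasedness statement to what the imputation supports.

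Either route needs revised wording and modest programming, with no new data collection. The gain is limited for Veterans who have no interim weights, so their number should be reported by arm.
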